**Figure 1 F1:**
[figure not shown]
Design of the trial.

The institutional review boards of The Netherlands Cancer Institute in Amsterdam, and the University Medical Center Utrecht have approved the study. This study follows the CONSORT guidelines
[27] and is registered at the Netherlands Trial Register (NTR3205) and ClinicalTrials.gov (NCT01562431).

### Study sample

The study sample will be composed of 264 counselees who request genetic counseling at either The Netherlands Cancer Institute in Amsterdam or the University Medical Center Utrecht. Counselees will be excluded from the study if they are younger than 18 years of age, do not have basic fluency in the Dutch language or are participating in another study that would interfere with the current study.

### Recruitment and randomization

All eligible counselees will receive an invitation letter from the family cancer clinic, an informed consent form, a baseline questionnaire, and a return envelope three weeks before their first counseling session. Upon returning the completed informed consent form and the baseline questionnaire, we will randomize the participants on a 1:1 basis to either the intervention group or the control group. The minimization method will be used to balance the intervention and control group for each counselor in terms of gender and the cancer syndrome for which genetic counseling is requested
[28]. Neither the counselees nor the counselors will be (or can be) blinded to group assigment.

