### Intervention group procedure

Within the Netherlands, individuals seeking cancer genetic counseling routinely undergo a first consultation with a genetic counselor or a clinical geneticist and, when opting for a DNA-test, a final counseling session during which the DNA-test results are disclosed to the counselee. If indicated, screening recommendations for the patient and relatives are discussed within these sessions. The study intervention will take place within this standardized process, at the time of the first face-to-face genetic counseling session (phase I), and by telephone 4 weeks after the final face-to-face counseling session (phase II). The participants in the intervention group will be asked to complete the PAHC questionnaire either via the internet or, if preferred, by mail shortly before the face-to-face and the telephone follow-up counseling sessions. The counselee’s responses to the PAHC questionnaire will be made available to the genetic counselor prior to the counseling sessions.

The PAHC questionnaire consists of 26 questions addressing psychosocial problems and worries that are specifically relevant to counselees within the cancer genetics counseling and testing setting. The content of the PAHC questionnaire is organized into the following six domains: (1) hereditary predisposition; (2) family- and social issues; (3) practical issues; (4) general emotional issues; (5) cancer-specific issues; and, for those who have children 6) children-specific issues. The number of items per domain varies between 2 and 7. All 26 items are scored on a 4-point, Likert-type scale ranging from 1 (“not at all”) to 4 (“very much”). The PAHC questionnaire is supplemented by the Distress Thermometer (DT), a visual analogue scale ranging from 0–10 (no distress-severe distress). The timeframe of the PAHC questionnaire and the DT is the previous week. Per problem domain assessed by the PAHC questionnaire, the respondent is asked to indicate whether (s)he would like to receive professional psychosocial support
[25].

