### Control group procedure

Counselees in the control group will complete the PAHC questionnaire and DT as described above for the intervention group. However, the results of these questionnaires will not be provided to the genetic counselors.

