**Counselees**		
*Baseline (first) questionnaire*	Cancer worries	Before randomization
	General distress	
	Demographic data	
*Second questionnaire (T1)*	Evaluation of screening instrument	4 weeks after genetic counseling, before final consult, end of phase I
	Evaluation of counselor	
	General distress	
	Need for extra support	
	Cancer worries	
*Third questionnaire (T2)*	Specific psychosocial problems	4 months after the telephone call,
	Need for extra support	end of phase II
	Cancer worries	
	Evaluation of screening instrument	
	Satisfaction	
	General distress	

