#### Specific psychosocial problems

The PAHC questionnaire will be used to assess (changes over time in) specific psychosocial problems experienced by counselees in both the intervention and the control group. This will be evaluated at both the individual item as well as the problem domain level.

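### In phase I the PAHC answers that serve as the yardstick for counselor awareness are collected after unblinded randomization, so the yardstick itself could differ by arm

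*Protocol article*

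**What the plan says.** Under Recruitment and randomization, the invitation, consent form and baseline questionnaire go out three weeks before the first session, and "Upon returning the completed informed consent form and the baseline questionnaire, we will randomize the participants on a 1:1 basis". The same section says that neither counselees nor counselors are blinded, and names counselor, gender and cancer syndrome as the minimization variables.

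Table 1 gives the content of the baseline questionnaire as cancer worries, general distress and demographic data, timed "Before randomization". The PAHC is not listed there.

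Under Intervention group procedure, the PAHC is completed over the internet or "by mail shortly before the face-to-face and the telephone follow-up counseling sessions". Under Control group procedure, "Counselees in the control group will complete the PAHC questionnaire and DT as described above for the intervention group", but "the results of these questionnaires will not be provided to the genetic counselors".

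Under Counselors' awareness, the counselor's rating in each of six domains is compared with the counselee's PAHC answers. Under Main research hypotheses, this becomes an absolute-agreement ICC per domain and arm, compared between arms by Fisher's r-to-z. Under Specific psychosocial problems, the PAHC has a second use: "The PAHC questionnaire will be used to assess (changes over time in) specific psychosocial problems".

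**The concern.** An agreement coefficient depends on both sets of ratings. The trial wants to know whether counselors perceive problems better when they receive the form. That requires the counselee's answers to mean the same thing in both arms. Here they are given after allocation. An intervention counselee's answers go to the counselor, with raised domains and requests for support marked in red; a control counselee's answers go nowhere clinical. If counselees know this when they answer, they may report more or less openly, spread their answers differently, or be more or less likely to return the form. The per-arm ICCs could then differ with no difference in counselor awareness.

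Non-return raises a related difficulty. All analyses are to be by intention to treat, yet agreement cannot be calculated for a counselee without a PAHC, and that loss would arise after allocation.

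The Methodological issues section discusses lack of blinding only as contamination through the counselors, which it calls conservative. A difference in answering is a separate route and need not be conservative.

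**Working it through.** **1. Order of events in phase I.** Consent and baseline questionnaire (no PAHC) → randomization → PAHC and Distress Thermometer in both arms → result printed and filed (intervention only) → session → counselor checklist. The PAHC therefore precedes the session but follows randomization. Cancer worries and general distress do have pre-randomization values; the PAHC and Distress Thermometer do not.

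**2. Arm sizes.** The plan's figure reproduces with a two-sided test: n = 2 × (1.96 + 0.8416)² / 0.4² = 98.1, so 99 per arm and 198 in total; 198 / 0.75 = 264, or 132 per arm at the start. The point does not affect this figure, which rests on the communication outcome. The arm sizes are used below.

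**3. Illustration for the ICC.** The protocol gives no ICC and no PAHC variance, so everything here is assumed. For two raters, let s² be the shared (true-score) variance, e² the error variance per rater and b the mean difference between raters. Then ICC = s² / (s² + e² + b²/2). Set s² + e² = 1 and a base ICC of 0.30 or 0.50 with b = 0. For the test, d = [atanh(ICC₁) − atanh(ICC₀)] × √((n − 3)/2), taken as positive, and the rejection probability is 1 − Φ(1.96 − d) + Φ(−1.96 − d).

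Three ways in which answering might differ in one arm:

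- *Mean shift* b of 0.2 or 0.4 SD. Example: 0.50 / (1 + 0.4²/2) = 0.50 / 1.08 = 0.46.
- *Wider spread in the counselee's answers only*, true-score part multiplied by k = 1.1 or 1.2: ICC = k s² / [(k² + 1) s²/2 + e²]. Example: 0.60 / (0.61 + 0.50) = 0.54.
- *Wider spread shared by both raters*, same k: ICC = k² s² / (k² s² + e²). Example: 0.72 / 1.22 = 0.59.

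| Difference in one arm | ICC from 0.30 to | Rejection, n = 99 to 132 | ICC from 0.50 to | Rejection, n = 99 to 132 |
|---|---|---|---|---|
| Shift 0.2 SD | 0.29 | 5.0% | 0.49 | 5.1% |
| Shift 0.4 SD | 0.28 | 5.3–5.4% | 0.46 | 6.3–6.7% |
| Counselee spread +10% | 0.32 | 5.3–5.4% | 0.52 | 5.5–5.7% |
| Counselee spread +20% | 0.34 | 6.0–6.3% | 0.54 | 6.7–7.3% |
| Shared spread +10% | 0.34 | 6.2–6.6% | 0.55 | 7.4–8.2% |
| Shared spread +20% | 0.38 | 9.8–11.5% | 0.59 | 14.5–17.8% |

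Worked case, bottom right: atanh(0.590) − atanh(0.50) = 0.678 − 0.549 = 0.129; times √(129/2) = 8.03 gives d = 1.03 and a rejection probability of 17.8%.

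**4. Reading the table.** The first four rows change only what the counselee writes, and rejection stays at 5% to 7%. The last two rows also need the counselor's ratings to follow the wider spread, which is a stronger assumption. If 25% of one arm and 30% to 40% of the other flagged a domain (assumed figures), the normal-scale shift is 0.15 to 0.42 SD, close to the first two rows. The shift rows assume that counselors and counselees otherwise rate at the same mean. Because b is squared, a standing offset in the same direction would enlarge the effect.

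**5. Which analyses use the phase I PAHC.** Awareness does, as reference. Discussion and referral are coded from audiotape, and service use is reported by the counselee. The problem hypothesis is tested by logistic regression on prevalence between arms, with specific problems listed at the third questionnaire; that test needs no starting value. Only a descriptive change over time would use the phase I PAHC as its start.

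**The case against.** The strongest reply is that the mechanism is not shown. The article says that counselees are unblinded but not when they learn their arm; if they learn it only at the session, the concern largely disappears. This stands, and the point is therefore conditional.

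Second, answering in the knowledge that the counselor will read the form may be part of the intervention as it would be used routinely. That is a fair defense for the communication outcome. It is weaker for awareness, where the form is the measuring instrument.

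Third, a simple rise in reporting moves an absolute-agreement ICC very little and, with no standing offset between raters, lowers it in the intervention arm, against the trial's hypothesis. This also stands for that mechanism.

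A reader might infer more: that the problem hypothesis lacks a valid baseline, that analyses among counselees with a reported need are compromised, or that all three primary outcomes are affected. The document does not support this. The planned test of that hypothesis is a between-arm comparison of prevalence, no need-based analysis is set out, and the other two primary outcomes do not take the PAHC as reference.

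**Conclusion.** The point holds in limited form. The order of events is clear from the text: the reference for one primary outcome is collected after unblinded allocation. A bias follows only if counselees know their arm when they answer and then answer or return the form differently; the document neither establishes nor excludes this. Its size cannot be computed. Under the assumptions above, rejection at a nominal 5% per domain stays at 5% to 7% when only the counselee's answers change and reaches up to 18% when both raters' spread widens by 20% at a base ICC of 0.50, so small to moderate is a reasonable expectation. No figure can be put on unequal return of the form. This is a worthwhile, inexpensive improvement confined to the phase I awareness outcome and any descriptive change from the phase I PAHC. It is not a flaw that undermines the trial.

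**What to change.** Change Recruitment and randomization so that the allocation is drawn, with the same minimization factors, once the phase I PAHC has been returned and before it is printed for the record. None of those factors depends on the PAHC, and the form must in any case be back before the session to be printed and filed. The phase I PAHC then becomes a pre-randomization measure in both arms and keeps its timing shortly before the session.

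If that window is too short, keep the draw where it is but do not tell the counselee the arm until the phase I PAHC has been returned. This removes the influence of known allocation on answering and return, though the measure remains formally post-randomization.

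Under either option, describe the phase II PAHC as a post-randomization measure.

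Cost: under the first option the draw falls within days of the session, which is tighter for forms sent by mail, and counselees who do not return the PAHC are not randomized, so somewhat more may need to be invited. The planned 99 per arm and 264 in total do not change.

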### Intervention group procedure

Within the Netherlands, individuals seeking cancer genetic counseling routinely undergo a first consultation with a genetic counselor or a clinical geneticist and, when opting for a DNA-test, a final counseling session during which the DNA-test results are disclosed to the counselee. If indicated, screening recommendations for the patient and relatives are discussed within these sessions. The study intervention will take place within this standardized process, at the time of the first face-to-face genetic counseling session (phase I), and by telephone 4 weeks after the final face-to-face counseling session (phase II). The participants in the intervention group will be asked to complete the PAHC questionnaire either via the internet or, if preferred, by mail shortly before the face-to-face and the telephone follow-up counseling sessions. The counselee’s responses to the PAHC questionnaire will be made available to the genetic counselor prior to the counseling sessions.

The PAHC questionnaire consists of 26 questions addressing psychosocial problems and worries that are specifically relevant to counselees within the cancer genetics counseling and testing setting. The content of the PAHC questionnaire is organized into the following six domains: (1) hereditary predisposition; (2) family- and social issues; (3) practical issues; (4) general emotional issues; (5) cancer-specific issues; and, for those who have children 6) children-specific issues. The number of items per domain varies between 2 and 7. All 26 items are scored on a 4-point, Likert-type scale ranging from 1 (“not at all”) to 4 (“very much”). The PAHC questionnaire is supplemented by the Distress Thermometer (DT), a visual analogue scale ranging from 0–10 (no distress-severe distress). The timeframe of the PAHC questionnaire and the DT is the previous week. Per problem domain assessed by the PAHC questionnaire, the respondent is asked to indicate whether (s)he would like to receive professional psychosocial support
[25].

The results of the PAHC questionnaire + DT will be printed and attached to the counselee’s medical record so that they are available to the genetic counselor prior to the relevant counseling session (face-to-face in phase I and telephone-based in phase II). To facilitate the genetic counselor’s rapid review of the questionnaire output, all problem domains for which the counselee responds “quite a bit” or “very much” to at least one item are color coded *red*, indicating a problem area that should preferably be discussed during the counseling session. All other problem domains, are color coded *green*, indicating that there is, in principle, no need to discuss it during the counseling. Additionally, based on the literature and analysis of a validation of the DT in a previous study by our group using a heterogeneous sample of counselees for cancer in the Netherlands, a score of 4 or greater on the DT is used to indicate a clinically relevant level of distress
[25,29]. Finally, the counselor will receive information about whether the counselee is interested in obtaining additional professional psychosocial support for any given problem area. Scores on the DT above the cut-off point, and counselees’ requests for additional psychosocial support are also color coded *red.* Additionally, to increase the ease of interpretation of the results, all items above the threshold will be printed in a bold font, and those items that are not above the threshold will be printed in light-grey. All counselors will receive written instructions/guidelines and training in the use of the PAHC questionnaire and the DT.

### Control group procedure

Counselees in the control group will complete the PAHC questionnaire and DT as described above for the intervention group. However, the results of these questionnaires will not be provided to the genetic counselors.

### Timing and content of study measures

Counselees will be asked to complete questionnaires at: (1) baseline, prior to randomization; (2) approximately 4 weeks following the first genetic counseling session, before the final counseling session takes place; and (3) approximately 4 months after the telephone-based counseling session.

The counselors will be asked to complete a baseline questionnaire at the start of the study, a checklist at the end of each counseling session, and a final questionnaire at the end of the study. Both the in-person and the telephone-based genetic counseling sessions will be audiotaped by two independent raters ([name]) for purposes of content analysis (see below). Inter-rater reliability will be assessed by double coding 10% of the audiotaped sessions, equally divided between the intervention group and control group sessions.

#### Sociodemographic and clinical data

The counselees’ age, gender, marital status, education level, number and age of children, and use of psychosocial services in the past and during the study, will be obtained via the self-report questionnaires (Table 
1). Data on whether (s)he was diagnosed with cancer in the past and, if so, at what age, whether there is a known gene mutation in the family, the counselees’ genetic test results, and the number of genetic counseling sessions will be extracted from the medical records.

**Table 1 T1:** Content and timing of study measures

	**Content of the measurement**	**Timing of measurement**
**Counselees**		
*Baseline (first) questionnaire*	Cancer worries	Before randomization
	General distress	
	Demographic data	
*Second questionnaire (T1)*	Evaluation of screening instrument	4 weeks after genetic counseling, before final consult, end of phase I
	Evaluation of counselor	
	General distress	
	Need for extra support	
	Cancer worries	
*Third questionnaire (T2)*	Specific psychosocial problems	4 months after the telephone call,
	Need for extra support	end of phase II
	Cancer worries	
	Evaluation of screening instrument	
	Satisfaction	
	General distress	
**Counselors**		
*Checklist*	Counselors’ awareness	After each counseling session and telephone call
*Baseline questionnaire*	Demographic data	Before the beginning of trial
*First questionnaire*	Evaluation of screening instrument	After finishing the trial
**Counselees and counselors**	Audio tapes	Genetic counseling
		Telephone call, 4 weeks after DNA-test disclosure

The counselors’ age, gender, and the number of years working at the family cancer clinic will be determined by questionnaire. (Table
1).

### Primary outcome measures

The primary outcomes of the trial are: (1) discussion of psychosocial problems; (2) counselors’ awareness of the counselees’ psychosocial problems; and (3) management of psychosocial problems during and after genetic counseling.

#### Discussion of psychosocial problems

Counselor-counselee communication about psychosocial issues will be assessed via content analysis of the audiotaped counseling sessions. Using a study-specific questionnaire, each counseling session will be coded for the specific psychosocial issues discussed during the counseling session. The coding reflects the 26 psychosocial issues of the PAHC questionnaire. Additionally, the percentage of counseling time devoted to the discussion of psychosocial issues will be calculated.

#### Counselors’ awareness

Counselors’ awareness of the psychosocial problems as experienced by their counselees will be assessed with a checklist completed by the counselors directly after the counseling sessions. The counselor will be asked to report whether (s)he believes that the counselee is experiencing problems in each of the 6 problem domains covered by the PAHC questionnaire on a 4-point scale ranging from (1, “no problem” to 4, “a severe problem”). The counselors’ ratings will be compared to the responses provided by the counselees on the PAHC questionnaire.

#### Management of psychosocial problems

The audiotapes of the counseling sessions will also be used to evaluate how the counselees’ psychosocial problems are managed. Specifically, the study-specific checklist will be used to code whether counselees were referred to additional sources of information about how to deal with psychosocial problems (e.g., websites or written materials) or to additional psychosocial counseling. The counselees will be asked to report their actual use of psychosocial services.

### Secondary outcome measures

Secondary outcomes include: (1) initiation of problem discussion; (2) the time devoted to discussing each psychosocial problem and the total duration of the counseling session; (3) cancer worries and general psychological distress; (4) cancer genetics-specific psychosocial problems; and (5) counselees’ and counselors’ satisfaction with the genetic counseling and with the intervention (the latter for the intervention group only).

#### Initiation of psychosocial issue discussion, and time devoted to such discussions

The audiotapes of the counseling sessions will be coded for who initiated the discussion of each specific psychosocial issue (i.e., the counselee or the counselor), the amount of time spent talking about psychosocial issues, and the total length of the counseling session.

#### Cancer worries and general psychological distress

Cancer worries will be assessed using an adapted version of the Cancer Worry Scale (CWS) as used in previous studies
[14,15,30]. The CWS is an 8-item questionnaire measuring the frequency of cancer worries, the impact of worries on mood, and the impact of worries on daily functioning.

The Hospital Anxiety and Depression Scale (HADS) will be used to assess general psychological distress
[31]. The HADS includes 14 questions and yields a total score, as well as subscale scores for anxiety and depression. It has been validated for use in the Netherlands
[32].

#### Specific psychosocial problems

The PAHC questionnaire will be used to assess (changes over time in) specific psychosocial problems experienced by counselees in both the intervention and the control group. This will be evaluated at both the individual item as well as the problem domain level.

